# Introduction:

Hypoglycemia is considered a limiting factor for insulin therapy in patients with diabetes mellitus type 1 and advanced diabetes type 2. Insulin-induced hypoglycemia not only causes symptomatic and sometimes temporarily disabling episodes but can be fatal. It also precludes the maintenance of euglycemia over a lifetime of diabetes and thus full realization of the benefits of glycemic control.

In healthy subjects the induction of hypoglycemia is followed by a coordinated hormonal response aimed at restoring normal blood glucose levels (1). Hypoglycemia results in suppression of endogenous insulin secretion from pancreatic β-cells and in increased secretion of counter regulatory hormones with glucagon and epinephrine being the first line response. All three of these physiologic defences may be defective in patients with type 1 diabetes rendering them at even increased risk for severe hypoglycemia (2). The lack of an adequate glucagon response to hypoglycemia occurs early in the course of type 1 DM and was first described by Gerich et al more than 30 years ago (3). In contrast to the defective epinephrine response, which is partially restored when hypoglycemic episodes are avoided, the impairment of the glucagon response is largely irreversible (4). The cessation of the adrenomedullary epinephrine response further promotes hypoglycemia-associated autonomic failure and hypoglycemia unawareness, thereby establishing a vicious cycle (2).

The most important stimulus for the pancreatic -cell to secrete glucagon in response to decreasing glucose concentrations has been found to be the resulting decrement in -cell insulin secretion. This has been concluded from studies demonstrating that both tonic stimulation of -cell insulin secretion by sulfonylureas and tonic inhibition of -cell insulin secretion by diazoxide impair the glucagon response to insulin induced hypoglycemia in healthy volunteers (5;6). According to this “insulin switch-off hypothesis” the impaired glucagon response during hypoglycemia in type 1 diabetes can be attributed to the intra-islet insulin deficiency and the resulting absence of a decrease in intra-islet insulin during hypoglycaemia (6).

Sulfonylureas, which are widely prescribed for the oral therapy of type 2 diabetes, act on ATP sensitive potassium channels (KATP), also referred to as sulfonylurea receptor or SUR1/Kir6.2. Binding of sulfonylureas to pancreatic -cell KATP channels results in closure of the channels, membrane depolarisation, calcium influx and exocytosis of insulin containing secretory granules.

The same KATP channels have recently been identified on glucagon secreting pancreatic -cells (7). Inactivation of KATP channels in isolated -cells by sulfonylureas resulted in enhanced glucagon secretion and results from islets isolated from SUR1 knockout mice suggest an important role for -cell KATP channels in the regulation of glucagon secretion (8-10). These results appear contradictory to those previously obtained in normal subjects and in patients with type 2 DM in whom sulfonylureas have been reported to suppress glucagon concentrations during insulin-induced hypoglycemia (11;12). However, a recent study performed type 1 diabetics without residual -cell function reported an increase of plasma glucagon concentrations following oral application of glibenclamide, a sulfonylurea drug (13).

These results suggest that -cell KATP channels are important regulators of glucagon secretion in patients with type 1 diabetes without residual -cell function. In this specific condition, the absence of intra-islet insulin may unmask direct stimulatory effects of sulfonylureas on -cell glucagon secretion. Therefore, we hypothesize that inactivation of -cell KATP channels by glibenclamide, a sulfonylurea compound, restores the defective glucagon response to insulin induced hypoglycemia in type 1 diabetics without residual -cell function, as indicated by unmeasurable C-peptide concentrations. Consequently, sulfonylureas, which are widely used as hypoglycemic agents in type 2 diabetes, may turn out to be useful tools in the prevention of insulin-induced hypoglycemia in patients with type 1 diabetes.

# Study objectives:

To demonstrate that oral administration of glibenclamide stimulates pancreatic glucagon secretion during hypoglycemia in insulin-deficient (C-peptide negative) patients with type 1 diabetes when compared to type 1 diabetic patients with residual insulin secretion (C-peptide positive).

# Study design and methods:

## General description of the study:

Patients with type 1 diabetes participating in this single-blind, randomized cross-over study evaluating the effect of glibenclamide on glucagon secretion during insulin induced hypoglycemia. Glucose and glucagon metabolism will be studied using an intravenous insulin infusion test. We anticipate that patients diagnosed with C-peptide negative type 1 diabetes will increase glucagon secretion after oral administration of glibenclamide compared to patients with type 1 diabetes with maintained residual -cell function.

## Study population:

Study subjects will be recruited according to the following criteria:

*Inclusion criteria for patients with type 1 diabetes*:

- Patients aged 18 to 50 years
- Patients diagnosed with C-peptide negative diabetes type 1 (C-peptide <200 pmol/L 6 min after 1 mg glucagon i.v. at plasma glucose concentrations between 5 and 11 mmol/l)
- Patients diagnosed with C-peptide positive diabetes type 1 (C-peptide > 500 pmol/l 6 min after 1 mg glucagon i.v. at plasma glucose concentrations between 5 and 11 mmol/l)
- Stable metabolic control; HbA1c levels <8.0 % and without episodes of antecedent severe hypoglycemias in the past four weeks

*Exclusion criteria*:

- Patients treated with medications potentially interfering with glucose metabolism, such as systemic steroids, immunosuppressive drugs (cyclosporine, tacrolimus, sirolimus), highly active antiretroviral therapy
- History coronary artery disease
- History of epilepsy or seizures
- Current smokers
- Any significant or unstable hepatic, cardiac, pulmonary, renal, neurological, musculoskeletal, hematological or endocrine disease.
- Pregnant or breast feeding women
- Woman of childbearing potential not using a reliable method of birth control such as oral contraceptives or IUD.
- Subjects refusing or unable to give written informed consent

## Study schedule:

### Patient recruitment:

Patients diagnosed with type 1 diabetes mellitus attending the outpatient clinic of the Division of Endocrinology, Diabetes and Clinical Nutrition at the University Hospital Basel will be asked to participate. Those deemed eligible will be given a detailed explanation of the study protocol. After written informed consent has been obtained, they will be invited to join a screening visit in our outpatient department. A total of 20 patients (10 patients per group) will be recruited.

### Screening visit

Patients eligible to participate will be asked to discontinue or taper long-acting insulin up to 24 h before the screening visit depending on the individual’s regimen. Short acting insulin will be used according to the patients’ individual regimen to keep plasma glucose concentrations within desired limits (5-11 mmol/l). All patients will be admitted to the outpatient clinic of the Division of Endocrinology of the University Hospital Basel ([name], Klinikum 2, ground floor) after fasting over night at 8 a.m. for approximately 90 min. A brief physical exam (including, blood pressure, heart rate, body weight and height, waist circumference) will be performed, and a baseline blood sample (including WBC, RBC, creatinine, electrolytes, C-peptide, HbA1c will be obtained). A pregnancy test will be obtained in women of childbearing potential.

Residual -cell function will be assessed by measuring plasma C-peptide concentrations in the basal state and 6 min after the intravenous administration of 1 mg glucagon (GlucaGen Novo Nordisk® 1 mg ampules) as previously described (14;15). Subjects with a C-peptide response < 200 pmol/l to intravenous glucagon will be considered as “C-peptide negative”. The glucagon stimulation test will only be performed at fasting glucose values between 5 and 11 mmol/l in order to receive reproducible test results and will be rescheduled otherwise.

*Assessment of autonomic neuropathy and hypoglycemia awareness:*

Participants will be screened for the presence of autonomic neuropathy by the assessment of heart rate variability through ECG recording during deep inspiration and expiration, a Valsalva manoeuvre and orthostatic testing. A baseline 12-lead ECG will be obtained in addition.

Hypoglycemia awareness will be assessed by the hypoglycemia awareness questionnaire (HAQ) and the Mood and Symptom Questionnaire (MSQ)(16;17). Additionally, patients will be asked to keep a diary for 7 days after inclusion into the study protocol overlooking their blood glucose level monitored at least four times daily in correlation with possible hypoglycemia associated symptoms.

### Intravenous insulin infusion study 1:

Patients eligible to participate in the study protocol based on the results of the screening visit will be asked to discontinue or taper long-acting insulin at least 24 h before the intravenous insulin infusion study. Short acting insulin will be prescribed on an individual basis in order to keep capillary glucose concentrations between 5 and 11 mmol/l. All patients will be admitted to the Clinical Research Center, University Hospital Basel ([name], Klinikum 2, 6th floor) between 8 and 9 p.m. for approximately **22 hours**, including an overnight stay. They will be asked to remain fasted after their regular dinner between 6 and 7 p.m. on the day of admission until the end of the insulin infusion study. **Patients will be under close supervision of a study physician throughout their inpatient stay.**

Two intravenous catheters will be inserted in antecubital veins and after a baseline blood sample has been obtained, an intravenous infusion of regular human insulin (10 Units Actrapid HM® in 50 ml normal saline) in will be started and continued overnight by means of a syringe pump (Braun perfusor® compact S). Adjustments based on blood glucose measurements every 15 to 60 min will be made to maintain blood glucose concentrations between 5 -8 mmol/l until the beginning of the experiment the next morning. The blood glucose will be stabilized at 5 mmol/l one hour before the onset of the intravenous insulin infusion study (see below). The intravenous line will be kept patent by infusion of a small amount of isotonic (0.9%) saline.

*Application of study drugs:*

At 7.30 a.m. all patients will receive 15 mg glibenclamide (3 tablets Daonil® 5 mg, Sanofi-Aventis Schweiz AG, 1217 Meyrin, Switzerland) or 3 placebo capsules (Doralgan Tabletten, Institute of Pharmacy, University Hospital Basel, 4031 Basel, Switzerland) with 200 ml of tap water in a randomized order. Glibenclamide plasma concentrations can be expected to peak ~ 2 hours after oral ingestion (18). Thereby, peak plasma concentrations will coincide with the glucose nadir during the insulin infusion study (see below).

*Randomisation procedure:*

A web-based random number generator ([www.random.org](http://www.random.org/)) will be used to assign a random number between 1 and 10 to each patient at the beginning of the first insulin infusion study. Those assigned an even number will receive glibenclamide during the first insulin infusion study and placebo pills during the second study. Patients assigned an odd number will receive the 2 therapies in reverse order.

*Insulin infusion and blood sampling:*

The intravenous insulin infusion test will be started at 8:30 a.m.. Regular human insulin will be infused at the rate of 30 mU/m²/min for 60 min and 15 mU/m²/min thereafter from 60 to 150 min in type 1 diabetics with a syringe pump (Braun perfusor® compact S) as previously described (19).. Venous blood samples will be taken at -30, -15, 0 min and at 5-10-min intervals over the next 150 min for the measurement of plasma glucose and at 15 min intervals for the measurement of plasma glucagon, epinephrine, metanephrine, growth hormone and cortisol concentrations. At the completion of the intravenous insulin study, the insulin infusion will be stopped, and 20% dextrose solution will be infused to re-establish normal glucose levels (4-8 mmol/l). The glucose infusion will be stopped when plasma glucose has stabilized >5 mmol/l for 30 min and a lunch will be served along with s.c. short acting insulin as needed. A total of 150 ml blood will be drawn during a metabolic stud

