### Intravenous insulin infusion study 2:

Patients will be asked to return for a second insulin infusion study within one month of the first study. All procedures will be identical as described above, except that subjects having received glibenclamide during the first insulin infusion study will receive placebo capsules and vice versa.

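### Treatment order is drawn separately for each patient, so nothing balances it within the two C-peptide groups of 10; a short stratified list would do so at almost no cost.

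*Protocol*

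**What the plan says.** The whole allocation procedure stands in the Protocol under 'Intravenous insulin infusion study 1', 'Randomisation procedure'. A web-based random number generator "will be used to assign a random number between 1 and 10 to each patient at the beginning of the first insulin infusion study". The rule for order follows: "Those assigned an even number will receive glibenclamide during the first insulin infusion study and placebo pills during the second study". Then: "Patients assigned an odd number will receive the 2 therapies in reverse order". No list, block, draw without replacement or stratification is stated.

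The surrounding design matters for how this works out:

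- 'General description of the study' calls it a "single-blind, randomized cross-over study evaluating the effect of glibenclamide on glucagon secretion during insulin induced hypoglycemia".
- 'Patient recruitment': "A total of 20 patients (10 patients per group) will be recruited".
- 'Study objectives' makes the contrast between C-peptide negative and C-peptide positive patients part of the aim.
- 'Screening visit' fixes C-peptide status before the first infusion study.
- 'Intravenous insulin infusion study 2': "Patients will be asked to return for a second insulin infusion study within one month of the first study".
- 'Data analysis' names analysis of variance and mentions neither period nor sequence.

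**The concern.** In a two-period cross-over each patient is his or her own control, so order matters only through a period effect. If as many patients take glibenclamide first as second, a period effect cancels from the mean treatment difference. If not, part of it stays in. If the imbalance differs between the C-peptide groups, part of it also enters the contrast between them, which the objective asks about.

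The protocol gives some reason to take a period effect seriously. Every second test follows a deliberately induced hypoglycaemia by at most a month. The Introduction says that the epinephrine response partly recovers when such episodes are avoided, and the entry criteria exclude recent severe episodes. This bears most on epinephrine, symptoms and glucose recovery, and less on glucagon.

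The point belongs to the protocol. A statistical analysis plan can add period to the model, but it cannot restore balance once patients have been allocated.

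**Working it through.** The protocol gives no figure for allocation balance, so there is none to reproduce.

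**Inputs.** n = 10 per group ('Patient recruitment'). Probability of glibenclamide first = 5 even numbers out of 10 = 0.5 ('Randomisation procedure'). Draws are taken as independent. π is the period effect (second minus first test); the documents do not give it.

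**Step 1: balance within a group.** The number k taking glibenclamide first is Binomial(10, 0.5).

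- Exactly 5:5: 252/1024 = 24.6%. Both groups: 0.246² = 6.1%.
- 7:3 or worse: 2 × (1 + 10 + 45 + 120)/1024 = 34.4%. At least one group: 1 − 0.656² = 56.9%.
- 8:2 or worse: 2 × (1 + 10 + 45)/1024 = 10.9%. At least one group: 1 − 0.891² = 20.7%.

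**Step 2: difference between groups.** The difference k1 − k2, shifted by 10, is Binomial(20, 0.5). It is at least 2 in absolute value with probability 50.3%, and at least 4 with 11.5%.

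**Step 3: shift if period is not modelled.** Within a group it is π(n − 2k)/n, in absolute size 0.2π at 6:4, 0.4π at 7:3 and 0.6π at 8:2. In the group contrast it is 2π(k2 − k1)/n, which is 0.4π for a difference of two patients and 0.8π for four.

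**Step 4: illustration on the glucagon scale.** Assume, since the documents are silent, that π is 5% to 20% of the 22 ng/l in 'Sample size calculation', so 1.1 to 4.4 ng/l. A 7:3 split then shifts the within-group result by 0.4 × 1.1 = 0.44 to 0.4 × 4.4 = 1.76 ng/l. The planned effect is 30% of 22 = 6.6 ng/l, so the shift is 7% to 27% of it.

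**Step 5: cost if period is modelled.** Let x = (n − 2k)/n, so |x| is 0.4 at 7:3 and 0.6 at 8:2.

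- *Period fitted separately in each group.* The variance of the treatment effect is multiplied by 1/(1 − x²): 1/0.84 = 1.19 at 7:3 and 1/0.64 = 1.56 at 8:2. At 6:4 it is 1/0.96 = 1.04.
- *One common period effect, other group at 5:5.* The within-group multiplier is 1 + 10x²/(10(1 − x²) + 10). At 7:3 this is 1 + 1.6/18.4 = 1.09; at 8:2 it is 1 + 3.6/16.4 = 1.22. For the group contrast the rise is half as large: 0.8/18.4 = 4% and 1.8/16.4 = 11%.

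**Step 6: with 8 evaluable per group** (the number in 'Sample size calculation' before the drop-out allowance). A split of 6:2 or worse has probability 28.9%, and a between-group difference of two or more has 45.5%. The problem stays about the same.

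**Step 7: would overall balance be enough?** With 10:10 forced over all 20 patients but no stratification, k in one group has probability C(10,k)·C(10,10−k)/C(20,10). A split of 7:3 or worse still has probability 17.9%, and the other group is then its mirror image. Stratification is what removes the difference between groups.

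**The case against.** The strongest reply is that simple randomisation is a valid method. Over repeated draws the expected shift is zero, and the multiples of π above hold only for particular splits. That stands. A reader might infer that the plan gives a biased estimate; the documents support only the narrower statement that one realised trial of this size will often be unbalanced.

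A reader might also take a period effect on the main results as given, for instance through practice on the cognitive tests. The documents do not support this. The primary endpoint is glucagon and the first secondary endpoint is glucose recovery; the cognitive tests can enter only through the further secondary endpoints. The protocol already plans alternate forms of the PASAT against learning, although it states no such measure for the CRTT. The Introduction describes the glucagon defect as mostly not reversible, so π may be small for the primary endpoint.

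The variance figures of 19% and 56% should not be read as the general cost. They need a separate period term in each group. A given group is 6:4 or better with probability 66%, and then the rise is at most 4%. The mean rise, leaving out 10:0 splits, is about 15%.

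Nor does the text show a failure of concealment. The draw comes after consent, screening and C-peptide classification, so the order does not yet exist when those decisions are made, and an independent draw cannot be predicted. What remains is small: the text does not say that the draw is logged or bar repeating it.

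Finally, a range of 1 to 10 matches 10 patients per group. If each number is used once per group, order is exactly 5:5. That is not the plain reading, but it is a possible one and the text should settle it.

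**Conclusion.** The point holds as an avoidable weakness of a stated procedure, at the level of a cheap improvement. The balance probabilities are exact, given independent draws and full groups of 10. The consequence is conditional: a shift proportional to an unknown period effect if that effect is left out of the model, or a modest loss of precision if it is included. Which of these applies depends on an analysis model that the protocol does not settle and that a statistical analysis plan may. The documents do not show that the glucagon result would be materially distorted.

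**What to change.** Replace the draw at the visit with a list generated and logged before the first patient. Stratify it by C-peptide group, with permuted blocks giving five glibenclamide-first and five placebo-first in each group. The hospital pharmacy holds the list and releases each order by patient number once eligibility and C-peptide group are fixed. Before drop-out, this makes the between-group difference in order zero and the variance multiplier 1.00. If the numbers 1 to 10 were meant to be used once each per group, the protocol should say so.

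The cost is a list of 20 entries and two small drawbacks. In a single-blind study, staff who know the earlier orders can deduce the last allocation or allocations in each group, whoever holds the list. This matters little, because every patient receives both treatments and group is set by C-peptide at screening. Drop-outs, which the sample size section expects, may also undo exact balance.

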***Restoration of s.c. insulin therapy and glucose monitoring***

**After completion of the insulin infusion study the patient’s glucose levels will be monitored every 30-60 minutes until 10 hours after the ingestion of the study drug. They will be discharged from the Clinical Research Center at 5:30 p.m.. The usual insulin regime will be resumed at a reduced dose for 24 hours (70% of the usual dose, see also below) to account for the potential increase in endogenous insulin secretion elicited by glibenclamide. If blood glucose values increase above 10 mmol/l using this approach, small dosages of short-acting insulin will be applied to decrease blood glucose levels to the desired range.**

*Assessment of hypoglycemia associated symptoms:*

To assess hypoglycemia associated symptoms, the Mood and Symptom Questionnaire (MSQ), the Complex Reaction Time Task (CRTT) and the Paced Auditory Serial Addition Task (PASAT) will be performed at baseline and every 30 minutes until restoration of euglycemic glucose levels (17;20;21).

The CRTT has been developed to measure sustained visual attention and psychomotor speed. During a 5 minute period participants have to respond to the presentation of coloured lights (which appear in random sequence) by pressing corresponding buttons as accurately and fast as possible. Using a PC based control algorithm the inter-stimulus intervals is shortened or lengthened, thereby modifying task difficulty so that subjects’ false response rate within a continuously moving window approaches 50 percent (20).

A computerized version of the PASAT will be employed as a measure of sustained and divided attention and executive function of the working memory. Pacing will be at 2.5 s intervals, total task duration will be 180 s. Subjects will be instructed to sum up the last to digits presented as fast and accurate as possible. Accuracy and verbal response time will be assessed. Several forms of the test will be used as to prevent simple learning effects (21).

*Safety measures:*

The subjects’ consciousness during the insulin infusion study will be rated using the Glasgow coma scale (GCS) rating system every 5 min after plasma glucose has dropped below 3.5 mmol/l. If the grading decreases below 3 for best eye response (eye opening to speech), 3 for best verbal response (inappropriate words), 4 for best motor response (withdraws from pain) or plasma glucose concentrations decrease below 1.5 mmol/l, the insulin infusion will be stopped or tapered and small amounts of glucose (5-10g or 25-50 ml of a 20% dextrose infusion) will be given intravenously until the GCS rating and plasma glucose have increased above the previously mentioned limits.

Due to the prolonged duration of action of glibenclamide and its potential glucose lowering effects in type 1 diabetics with residual -cell function, patients will be instructed to taper their usual insulin dose **by 30 %** and monitor their capillary blood glucose every two to four hours and any time after the onset of symptoms suggestive of hypoglycemia for 24 hours after oral application of glibenclamide. They will be asked to ingest 10 grams of oral dextrose if capillary blood glucose concentrations drop below 4.0 mmol/l. When ever correction of blood glucose levels < 4.0 mmol/l becomes necessary, a repeat glucose measurement will be performed after one hour. All participants will be provided with the phone number of a study investigator in case any problems should arise after discharge from the clinical research center. **All patients will be advised to refrain from vigorous physical activity and driving motor vehicles within 24 hours after the ingestion of the study drugs**. **Furthermore, patients will be advised to increase the dosage of short acting insulin if blood glucose readings exceed 10 mmol/l.**

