## Potential risks and adverse events:

### Potential risks:

We consider the risks of this study to be mild. The specific risks are as follows:

Blood Loss: The total blood loss for this study will be approximately 300 ml.

Intravenous Catheters: Intravenous catheters used during the study are associated with a mild to moderate degree of pain upon insertion, and a small risk of localized infection.

Intravenous glucagon stimulation test: From our own experience the intravenous injection of glucagon is frequently associated with short-lasting (2-3 min) nausea and abdominal discomfort. Further side effects include vomiting, abdominal pain, paradoxic hypoglycemia, bradycardia (frequency 1:100 – 1:10’000) an rarely (frequency <1:10’000) with hypersensitivity, allergic reactions, hypoglycemic coma, tachycardia, hypotension, hypertension.

Intravenous insulin infusion: The intravenous insulin infusion is a safe technique which has been extensively used for the assessment of hypoglycemia counter regulation in type 1 diabetics (19). During the induction of hypoglycemia the subjects will be under close medical supervision. No long-term health effects can be anticipated from the induction of a short period of hypoglycemia. All infusions will be prepared under sterile conditions.

Insulin induced hypoglycemia following a bolus injection of regular human insulin (0.1-0.15 IU/kg body weight) is regularly used as a standard diagnostic procedure for the assessment of the hypothalamo-pituitary-adrenal axis and pituitary growth hormone secretory function at our institution. Venous plasma glucose concentrations between 1.5 and 2.0 mmol/l are regularly achieved during this procedure. Based on previous studies, the glucose nadir during our study can be anticipated to be around 2.0 mmol/l (40 mg/dl) (19). The insulin infusion will be discontinued or tapered if the plasma glucose concentration decreases below the threshold of 1.5 mmol/l (30 mg/dl) or significant impairment of consciousness occurs at any time point of the experiment (see section 3.3.3 – safety measures).

To minimize the potential risks associated with profound hypoglycemia, patients with a history of epilepsy, seizures and coronary disease are not eligible to participate. The upper age limit of 50 years and the exclusion of current smokers and patients with inadequate glycemic control (HbA1c > 8%) further minimizes the risk of silent coronary disease which may become clinically apparent during hypoglycemia.

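### After a coma-scale trigger the rescue rule lets the experimental insulin be tapered instead of stopped, and nothing ends the test for that patient

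*Protocol*

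**What the plan says.** The rule stands in the Protocol under Safety measures, within Intravenous insulin infusion study 1. Consciousness is rated every 5 min once plasma glucose is below 3.5 mmol/l. There are two kinds of trigger. One is the coma scale: "If the grading decreases below 3 for best eye response (eye opening to speech"), with matching limits of 3 for the verbal and 4 for the motor response. The other is plasma glucose below 1.5 mmol/l. Either one leads to the same action: "the insulin infusion will be stopped or tapered and small amounts of glucose" (5-10 g), which "will be given intravenously until the GCS rating and plasma glucose have increased above the previously mentioned limits".

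The section Potential risks restates the rule: "The insulin infusion will be discontinued or tapered if the plasma glucose concentration decreases below the threshold of 1.5 mmol/l", or if "significant impairment of consciousness occurs at any time point of the experiment".

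The scheduled infusion runs at the higher rate for 60 min and at the lower rate "thereafter from 60 to 150 min in type 1 diabetics". Full restoration is described only for the end of the test: "At the completion of the intravenous insulin study, the insulin infusion will be stopped, and 20% dextrose solution will be infused" to bring glucose to 4-8 mmol/l. The dextrose ends once glucose has been stable above 5 mmol/l for 30 min. On supervision, the Protocol states: "Patients will be under close supervision of a study physician throughout their inpatient stay".

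Intravenous insulin infusion study 2 asks patients back within one month for the same procedures with the study drugs swapped. It states no exception on safety grounds.

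**The concern.** A glucose reading below 1.5 mmol/l in a responsive patient and a loss of responsiveness are different events. For the first, lowering the pump rate is a reasonable way to steer the glucose. For the second, the same wording permits the agent that caused the event to keep running at a reduced rate in a patient who may no longer open the eyes to speech. No rate, criterion or time limit says when tapering is acceptable.

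What is at stake is the safety of an individual patient in an experiment that induces hypoglycemia on purpose. Two decisions after such an event are left to the moment: whether insulin stops, and whether the test goes on. A third, whether the patient should face the same test again, is not addressed. A patient-level stopping rule belongs in the protocol and is not something usually left to a statistical analysis plan. Here the rule is present, but it fixes the more serious of its two cases badly.

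**Working it through.** The plan gives no figure to reproduce, so the check sets the relevant provisions side by side.

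1. **Trigger and action.** Safety measures joins the coma-scale limits (eye 3, verbal 3, motor 4) and the glucose limit (1.5 mmol/l) with *or* and gives one action for both. Potential risks does the same and names impaired consciousness expressly. The taper option therefore covers the coma-scale event in both places; it is not a slip in one of them.

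2. **Where the rescue ends.** Glucose is given until the rating and plasma glucose are above the trigger limits. On glucose, that target is 1.5 mmol/l. The lower end of the restoration range is 4 mmol/l, so the rescue may end 4 - 1.5 = 2.5 mmol/l short of it. The section Potential risks anticipates a nadir of around 2.0 mmol/l in this test. That is only 2.0 - 1.5 = 0.5 mmol/l above the rescue limit, so a patient just past the limit is still at the level the experiment aims for.

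3. **Where the test ends.** The only fixed end is 150 min. Restoration to 4-8 mmol/l follows completion of the test, and nothing says that a trigger counts as completion.

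4. **Other provisions that might require a stop:**
   - Close physician supervision (Intravenous insulin infusion study 1): a safeguard, but without a criterion for stopping.
   - Attribution of Adverse Events, and the 48-hour reporting of serious events: classification and reporting, not management of the patient.
   - Data and safety review: weekly, and about whether the study continues or its documents change, not about one patient's test.
   - Informed consent: withdrawal at any time, at the patient's own choice.

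   None of them requires insulin to stop or the test to end.

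5. **Second test.** The stated difference from the first is the swap of study drug. The entry criterion of no severe hypoglycemia in the past four weeks applies at inclusion, and the Protocol does not say that it is checked again before study 2.

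Together, a patient could trigger on the coma scale, receive 5-10 g of glucose, recover just past the limits, continue on reduced insulin to 150 min and be asked back within a month, all in line with the written rule.

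**The case against.** The strongest reply is that the hazard is treated. Intravenous glucose is not optional and continues until both consciousness and glucose are above their limits. Consciousness is rated every 5 min, glucose is measured every 5-10 min, and a physician is in close attendance. Only the pump setting is left to that physician, who would very probably stop the insulin. This is fair, and it rules out the reading that the Protocol leaves an unresponsive patient untreated or keeps insulin running by design. Stopping is one of the two named options. What stands is that it is not the required one.

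A second reply is that tapering has a rationale: long-acting insulin has been withdrawn or tapered, and one group is C-peptide negative, so the infusion may be the patient's main insulin supply. But the Protocol stops the infusion for every patient at 150 min, so stopping is already part of the procedure.

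Third, a reader might infer that the second test follows automatically. The text does not support that. Patients are asked to return and may withdraw, and a serious event would come before the weekly review. The supported statement is narrower: no safety exception is stated for study 2. Nor is the four-week entry criterion breached, since it governs inclusion.

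Finally, one might try to size the problem by the insulin still scheduled after a trigger. That would be the untapered dose at an assumed trigger time, with the rescue glucose ignored. It measures neither what tapering allows nor the risk.

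**Conclusion.** The point holds in this form: the written rule does not require insulin to be stopped, or the test to be ended, after a coma-scale trigger or significant impairment of consciousness, and its rescue target is the trigger limit instead of normal glucose. The absence of a safety exception for study 2 is a secondary point.

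The size cannot be expressed as a number of patients. The Protocol gives no frequency for the event among the 20 patients planned, and none is assumed here. The event is presumably rare and the attending physician would probably act correctly, so this is a change that should be made and not a reason to regard the study as unsafe. It weighs enough to act on because the preferred action is clear, the possible harm is serious and the correction is small. The conclusion rests on the wording of the Protocol alone. It would fall if another binding study document already required a stop.

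**What to change.** For the coma-scale or impaired-consciousness trigger only:

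- In Safety measures, delete the option to taper, so that insulin is stopped. In Potential risks, replace the choice between discontinuing and tapering by stopping.
- State that the test ends for that patient and that the existing end-of-test restoration starts at once: 20% dextrose until plasma glucose has been stable above 5 mmol/l for 30 min.
- In Intravenous insulin infusion study 2, add that a patient with a coma-scale trigger in study 1 does not proceed to study 2. A plain bar is better than a choice between omission and delay, which would again leave the decision open.

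The rule for glucose below 1.5 mmol/l without a coma-scale trigger stays as it is, so the experiment is unchanged for everyone else.

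The cost is a short amendment with no new procedure, visit or sample. The affected patient's data after the trigger are lost and, if the trigger falls in study 1, so is that patient's paired comparison. Part of that loss exists already, because rescue glucose disturbs the 0-150 min glucagon curve and the 60-150 min glucose recovery. The sample size section requires 8 and recruits 10 per group, a margin of 10 - 8 = 2, but that margin is meant for drop-outs of every kind and is not reserved for this.
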